#### 2.8.2. Pharmacodynamic Data Analysis

The absolute values and changes from baseline urine and plasma concentrations of thymidine and deoxyuridine will be calculated using Day 0 or Day 1 as the baseline. The proportion of patients who achieve metabolic correction (plasma thymidine <3 µmol/L and deoxyuridine <5 µmol/L) will be presented by dose. The activity of thymidine phosphorylase administered will be calculated for each treatment cycle and longitudinal changes will be plotted. The presence of specific anti-thymidine phosphorylase antibodies will be recorded.

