### 2.3. Trial Design

The trial is a Phase 2, multi-centre, multiple dose, open label trial without a control which will be conducted in a maximum of five sites in Europe and Israel, with all patients receiving EE-TP. For each patient, the overall study duration will be 31 months, consisting of a 28 day screening phase, a 90 day run-in phase, a 24 month open-label treatment phase, and a 90 day follow-up phase. A schematic of the proposed study design is presented in Figure 2.

Patients will be screened for eligibility from Day −120 to Day −92. If eligible, patients will then enter the run-in period, from Day −91 to pre-dose on Day 0, in which key aspects of their overall clinical condition and metabolite levels will be recorded. The variability in these clinical and metabolic parameters is currently unknown, and these data will primarily serve to act as each patient’s own pre-treatment/control observations.

Prior to entering the treatment phase, patients will attend the study site for pre-treatment assessments and to determine continued study eligibility either the day before dosing (Day –1) or in the morning of the day of dosing (Day 0). For the first four treatment cycles, the administration will be every 21 days, with the administration of EE-TP at the same time of day (±2 h). The first dose (Treatment Cycle 1) of EE-TP will be administered on day 0, with subsequent doses on Days 21, 42, and 63 (Treatment Cycles 2, 3 and 4, respectively). For Treatment Cycles 1, 2, 3, and 4, patients will leave the study site following dosing and return the next day (Days 1, 22, 43, and Day 64, respectively) for 24 h post-dose assessments. The planned dose levels are presented in Table 2. All patients will receive infusions at Dose Level 1 (~58–65 × 10^10^ erythrocytes encapsulating ~30–49 U TP/10^10^ erythrocytes) for the first 2 treatment cycles (Treatment Cycles 1 and 2). If metabolic correction (defined as plasma thymidine <3 µmol/L and deoxyuridine <5 µmol/L, i.e., below the diagnostic levels for MNGIE) is not achieved, the subsequent 2 treatment cycles (Treatment Cycles 3 and 4) will be administered at Dose Level 2 (~58–65 × 10^10^ erythrocytes encapsulating ~50–69 U TP/10^10^ erythrocytes).

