### 2.8. Statistical Analyses

Statistical analyses will be primarily descriptive. Analyses will be performed using Statistical Analysis Software^®^ (Version 9.2 or higher, SAS Institute, Cary, NC, USA). For continuous data, summary statistics will include the arithmetic mean, arithmetic standard deviation, median, lower and upper quartiles, plus minimum, maximum, and number. For log normal data, summary statistics, including the geometric mean and geometric coefficient of variation, will also be presented. For categorical data, frequency counts and percentages will be presented. Data listings will be provided for all patients up to the point of withdrawal, with any patients excluded from the relevant population indicated. For the calculation of summary statistics and statistical analysis, unrounded data will be used.

For each study participant the change from baseline will be calculated by subtracting their mean baseline value from the value at the specific time point. The mean change from baseline will be derived as the arithmetic mean of all individual patients’ change from baseline values.

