Plasma thymidine and deoxyuridine			X	X	X		X	X	X		X	X	X		X	X	X ^4^	X
Urine thymidine and deoxyuridine	X		X	X	X		X	X	X		X	X	X		X	X	X ^5^	X
Body weight and height																	X	X
BMI																	X	X
Handgrip dynamometer													X				X	X
RODS													X				X	X
10-metre walk test													X				X	X
EuroQol-5D													X				X	X
PGIC													X				X	X
CGI-I													X				X	X
PROMIS													X				X	X
VAS symptom													X				X	X
TPN use													X				X	X
Neurological examination																	X	X
MRI (brain)																	X ^6^	X
Abdominal ultrasound																	X ^6^	X
Nerve conduction and electromyography ^7^																	X ^6^	X
Neuro-ophthalmological assessment																	X ^6^	X
FGF21, GDF15, and other markers of mitochondrial condition		X	X	X	X	X	X	X	X	X	X	X	X	X	X	X	X	X

^1^ Female patients only will be assessed at every 4 weeks. ^2^ Medication will be assessed for potential mitochondrial toxicity. ^3^ As reported in Table 4. ^4^ For the first 6 months, patients will return for an additional analysis of plasma thymidine and deoxyuridine at 7 days post-dose of every other treatment cycle. For rest of dosing, patients will return for an additional analysis of plasma thymidine and deoxyuridine at 7 days post-dose once every 4 treatment cycles. ^5^ 24 h urine collection for creatinine, thymidine, and deoxyuridine excretion will start from 6 days post-dosing for 24 h at every 4 treatment cycles. ^6^ Performed at 12 and 24 months. ^7^ As reported in Table 3. TC—treatment cycle.

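### The pharmacodynamic baseline may be Day 1, a post-dose day with no metabolite sample scheduled, and the rule does not fit the scheduled pre-dose samples

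*Protocol article*

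**What the plan says.** Section 2.8.2 (Pharmacodynamic Data Analysis) states that "changes from baseline urine and plasma concentrations of thymidine and deoxyuridine will be calculated using Day 0 or Day 1 as the baseline". It gives no rule for choosing between the two days.

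Section 2.3 (Trial Design) fixes the timing: "The first dose (Treatment Cycle 1) of EE-TP will be administered on day 0". After each of the first four doses patients "return the next day (Days 1, 22, 43, and Day 64, respectively) for 24 h post-dose assessments". The last pre-treatment visit is on Day −1 or the morning of Day 0. Of the clinical and metabolic data collected in the run-in, the same section says that "these data will primarily serve to act as each patient’s own pre-treatment/control observations", and Section 3 (Discussion) repeats this.

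Section 2.8 gives the general rule that "the change from baseline will be calculated by subtracting their mean baseline value from the value at the specific time point". Section 2.8.3 takes the run-in period, Day −91 to Day 0, as the baseline for efficacy.

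**The concern.** A baseline has to precede treatment, and Day 1 does not. The rule also names days that do not match the sampling schedule, and it departs from the run-in baseline that the rest of the article builds towards.

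Pharmacodynamics is among the primary objectives (Section 2.1). The trial has no control arm, so each patient's own pre-treatment level is the only comparator for the fall in thymidine and deoxyuridine. An unclear baseline leaves three questions open: which value is subtracted, whether it is the same kind of value in every patient, and whether part of the treatment effect has already been absorbed into it.

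**Working it through.** The article states no figure for this point, so there is none to reproduce. The main check sets the rule against the schedule.

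**Step 1. When metabolites are sampled (Tables 3 and 4).** The Table 4 row "Plasma thymidine and deoxyuridine" and the urine row below it each align with all 18 columns.

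| Time | Plasma | Urine | Relation to first dose |
|---|---|---|---|
| Day −91 to −84 (Table 3) | yes | yes | before |
| Mid run-in (Table 3) | yes | yes | before |
| Day −1 to 0 (Table 3) | yes | yes | before |
| Day 0 (Table 4) | no | yes | day of dosing |
| Day 1 (Table 4) | no | no | 24 h after |
| Day 7 (Table 4) | yes | yes | after |

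A Day 1 visit does take place, and FGF21, GDF15 and related markers are scheduled then, but thymidine and deoxyuridine are not.

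**Step 2. Applying the rule as printed.**

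- Day 1 as baseline: no scheduled value exists for plasma or urine, and 0 of the 3 run-in values are used.
- Day 0 as baseline, plasma: the only candidate is the Table 3 sample for Day −1 to 0, and only if it is taken on Day 0. At most 1 of the 3 run-in values is used.
- Plasma sample taken on Day −1: the patient has no plasma value on Day 0 or Day 1, so the rule yields no baseline.

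**Step 3. What a Day 1 value would do if one were taken and used.** Let f be the Day 1 level and g the later on-treatment level, each as a fraction of the pre-dose level. The true absolute fall is 1 − g, the fall measured from Day 1 is f − g, and the share captured is (f − g)/(1 − g). The documents give neither f nor g, so all values below are assumptions.

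| f | Share captured, g = 0.25 | Share captured, g = 0.10 |
|---|---|---|
| 1.00 | 0.75/0.75 = 100% | 0.90/0.90 = 100% |
| 0.90 | 0.65/0.75 = 87% | 0.80/0.90 = 89% |
| 0.75 | 0.50/0.75 = 67% | 0.65/0.90 = 72% |
| 0.50 | 0.25/0.75 = 33% | 0.40/0.90 = 44% |

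A pre-dose baseline captures 100% in every row.

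**Step 4. One baseline value against the mean of three.** With independent within-patient errors of variance s² and no drift over the run-in, the error variance of a change is s² + s² = 2s² from a single baseline value. From the mean of three it is s² + s²/3 = 1.33s². The ratio is 0.667, so variance is 33% lower. The standard error ratio is √0.667 = 0.816, about 18% lower.

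**The case against.** The strongest reply is that Day 1 is a misprint for Day −1. Section 2.3 and Table 3 both pair Day −1 with Day 0 as the last pre-dose visit, so the intended rule may simply be the last pre-dose value within a one-day window. That is plausible. Minus signs survive elsewhere in the text, so loss in reading the PDF is less likely, but it cannot be excluded. On that reading the post-dose problem disappears. The sentence still needs correcting, and it would still rest on a single value.

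A reader might infer that the metabolite fall in this trial will be understated by some known amount. The documents do not support that: no Day 1 metabolite sample is scheduled, and the first-day fall is not given. Step 3 is illustration only.

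A reader might also infer that all three run-in values are discarded. That is too strong, because the third is the Day −1 to 0 sample and can serve as a Day 0 baseline.

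It is fair, too, that the last pre-dose value is a common and valid baseline, and that a specific pharmacodynamic rule may differ deliberately from a general one. Section 2.8 does not say over which visits its mean is taken, and calling run-in data a control does not in itself define an analysis baseline. The passages fit poorly together, but this part falls short of a flat contradiction. The gain in Step 4 assumes independent errors and no drift, whereas Sections 2.3 and 3 say that run-in variability is not known. Preferring the mean is therefore partly a judgement.

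Finally, the analyses are mainly descriptive. Metabolic correction, which also governs dose progression, is defined by absolute thresholds (thymidine below 3 µmol/L and deoxyuridine below 5 µmol/L) and does not depend on the baseline.

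**Conclusion.** The point holds in a limited form. Section 2.8.2 names as a possible baseline a day that follows the first dose and has no metabolite sample. For plasma, the rule also fails for any patient whose last pre-dose sample is taken on Day −1. This follows from the text and tables alone, and the sentence needs correcting even if Day −1 was meant.

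The size of any bias is unknown. It would arise only if an unscheduled Day 1 sample were taken and used, and it would then equal the first-day fall. The precision lost by using one run-in value instead of three is at most moderate (standard error ratio 0.816 under the Step 4 assumptions). The defect affects the change-from-baseline summaries of plasma and urine thymidine and deoxyuridine. It does not affect their absolute values, the proportion with metabolic correction, or the dose-progression criterion.

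**What to change.** In Section 2.8.2, delete Day 1 and define the baseline from scheduled pre-dose samples only. Suggested wording: *For plasma and urine thymidine and deoxyuridine, baseline is the mean of the patient's run-in values (Day −91 to −84, mid run-in, and Day −1 or Day 0 before the first infusion). Change from the last pre-dose value (Day −1 or Day 0) will also be shown.*

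The run-in mean is preferred because it agrees with the role given to the run-in in Sections 2.3 and 3 and with the averaged baseline in Section 2.8. If the sponsor prefers the last pre-dose value, naming Day −1 or Day 0 before infusion would also remove the error. Table 4 should state that the Day 0 urine sample is taken before the infusion, if it is to count towards baseline.

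The cost is one sentence and, if needed, one table note. All the samples are already scheduled, and Section 2.13 says that recruitment has not opened, so no collected data would be affected.

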#### 2.4.1. Study Inclusion Criteria

Patients must be aged 18 years or older. The age range will be extended to include:
(i)Patients aged 16 years or older after 24 patient-months of exposure in those aged 18 years or over;(ii)Patients aged 12 years or older after 24 patient-months of exposure in patients aged under 18 years of age at the time of enrolment.Patients must be diagnosed with MNGIE by demonstrating all of the following:
(i)<18% normal thymidine phosphorylase activity in the buffy coat;(ii)>3 μmol/L plasma thymidine;(iii)>5 μmol/L plasma deoxyuridine;(iv)Confirmation of the presence of biallelic pathogenic variants in TYMP by sequencing.Patients must be able to undergo study procedures.Patients must agree to either remain completely true abstinent or to use 2 effective contraceptive methods from Screening until completion of the Follow-up Visit.Patients must be willing to sign and date the written Informed Consent Form.

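### The metabolic correction cut-offs equal the entry cut-offs and the proportion uses no run-in value, so a patient near both cut-offs can count as corrected without a drug effect, with no untreated rate for comparison

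*Protocol article*

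**What the plan says.** All references are to the protocol article.

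- **Entry (Section 2.4.1).** Among other criteria, all of which must be met, a patient needs ">3 μmol/L plasma thymidine" and ">5 μmol/L plasma deoxyuridine".
- **Correction (Section 2.3).** It is "defined as plasma thymidine <3 µmol/L and deoxyuridine <5 µmol/L, i.e., below the diagnostic levels for MNGIE". Section 2.8.2 repeats the numbers for reporting: "The proportion of patients who achieve metabolic correction (plasma thymidine <3 µmol/L and deoxyuridine <5 µmol/L) will be presented by dose". Neither section attaches a minimum fall, a repeat sample or a comparison with pre-treatment values.
- **Plasma baseline (Section 2.8.2).** Changes in thymidine and deoxyuridine are taken from Day 0 or Day 1. Section 2.8.3, by contrast, uses the whole run-in as baseline for efficacy.
- **Sampling.** Table 3 has plasma metabolites at screening and at three run-in points. Table 4 has none on Day 0 or Day 1. It then has 11 by Day 77 (Days 7, 14, 21, 28, 35, 42, 49, 56, 63, 70 and 77) and more to Month 24.
- **Purpose of the run-in (Section 2.3).** It provides each patient's own control data, because "The variability in these clinical and metabolic parameters is currently unknown".

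**The concern.** The line a patient must be above to enter is the line the patient must be below to count as corrected. Nothing in the definition separates a real fall from ordinary variation around that line. The run-in was built to measure that variation, yet the reported proportion makes no use of it.

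The stated baseline does not repair this. Day 1 comes after the first dose, and Table 4 marks no plasma sample on either day. At best, the last run-in visit in Table 3 (Day −1 to 0) supplies one pre-dose value, and the other two run-in samples go unused.

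The article treats BMI differently. The Discussion chooses a minimum gain of 0.2 kg/m² partly because it probably exceeds within-person variation. The metabolite proportion has no such margin.

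Pharmacodynamics is a primary objective (Section 2.1), there is no control arm (Section 2.3), and 12 adults are planned (Section 2.7). One false responder moves the proportion by 1/12 = 8.3 percentage points. A reader would have no untreated rate to set it against.

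**Working it through.** The article states no expected correction rate, so there is no figure to reproduce. The question is how often a patient with a constant true level and no drug effect would meet the rule.

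**Inputs from the article:** cut-offs 3 and 5 µmol/L, both analytes required; 11 plasma samples by Day 77 (Table 4); 3 run-in samples (Table 3).

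**Assumed, because the article gives none:** log-normal values; true median of each analyte = r × its cut-off; within-patient CV 20% (range 10–30%); correlation between analytes 0.8 (range 0–0.8); independent samples; any one sample below both cut-offs counts.

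**Formulas**

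- Log-scale SD: σ = √ln(1 + CV²) = √ln(1.04) = 0.198.
- Standardised distance to the cut-off: z = −ln(r)/σ.
- Chance that one sample meets the rule: p = Φ₂(z, z; ρ), the bivariate normal probability that both analytes are below.
- Chance of at least one such sample in n: 1 − (1 − p)ⁿ.

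**Results at CV 20%, correlation 0.8**

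| r | z | p, one sample | any of 3 | any of 11 | two in a row among 11 |
|---|---|---|---|---|---|
| 1.1 | −0.481 | 22.4% | 53.3% | 93.9% | 35.7% |
| 1.25 | −1.127 | 7.7% | 21.3% | 58.5% | 5.4% |
| 1.5 | −2.047 | 0.86% | 2.6% | 9.1% | 0.07% |
| 2 | −3.500 | <0.01% | about 0% | 0.05% | about 0% |

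Example for r = 1.25: 1 − (1 − 0.0769)¹¹ = 0.585.

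**Range for any of 11, over CV 10–30% and correlation 0–0.8:** 27–97% at r = 1.1; 0.2–83% at 1.25; 0–40% at 1.5; 0–3.7% at 2.

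Two things follow. First, the effect is large only when both analytes lie close to their cut-offs: within about 25%, or about 50% if the CV is 30%. Second, the columns for 3 and 11 samples differ widely for the same untreated patient (21.3% against 58.5% at r = 1.25). An ever-corrected rate in the run-in therefore cannot be compared directly with an ever-corrected rate on treatment. The rate per sample can.

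**The case against.** **Near-threshold patients may never be enrolled.** This stands as a limit on size. The article gives no baseline metabolite levels. A reader might infer such patients from the entry rule "<18% normal thymidine phosphorylase activity in the buffy coat", since the Introduction describes the disease as below 10% of normal. But that is enzyme activity, not metabolite level, and entry also requires both metabolites above the cut-offs and biallelic *TYMP* variants. The criterion makes milder patients possible and does not show that any will enter.

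**The article does not say that any single later sample suffices, or that entry rests on one value.** Correct. Both would be inferences: Section 2.8.2 does not name the deciding sample, and Table 3 shows one screening visit without the number of samples. The full protocol or analysis plan may settle both. The 11-sample figures hold only under the any-sample reading. Positive correlation between successive samples would lower them.

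**There is a pre-dose check.** A reader might infer that the run-in is ignored altogether. It is not: metabolites are measured three times, and sites "determine continued study eligibility either the day before dosing (Day –1) or in the morning of the day of dosing (Day 0". What can be said is narrower. The article does not state that the metabolite cut-offs are re-tested then, and Table 3 marks the inclusion and exclusion criteria at screening only.

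**Absolute values, changes and listings would expose a trivial fall.** Largely true for a careful reader of 12 patients. It does not supply an untreated rate for the proportion, and the changes start from a baseline that uses at most one of the three run-in samples.

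**Falling below the diagnostic level is a legitimate target.** Agreed. That is a reason to keep the definition and add a reference rate beside it.

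**Conclusion.** The point holds as a weakness in how the proportion is reported. The entry and correction cut-offs are the same numbers, no run-in value enters the proportion, and the stated plasma baseline falls on days for which Table 4 schedules no plasma sample, one of them after dosing. A patient with both analytes near the cut-offs can be counted as corrected without a drug effect, and the plan offers nothing against which to judge how often.

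The documents do not support saying that such patients are or will be counted. The practical size is unknown: serious if some adults enter within about 25% of both cut-offs, negligible if all enter at twice the cut-offs or more. The run-in samples can show which case applies, and that is the main reason to use them.

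**What to change.** In Section 2.8.2, for reporting only:

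1. Apply the same <3 and <5 µmol/L rule to the three run-in plasma samples. Report the untreated rate per sample beside the on-treatment rate per sample. Leave the screening sample out, because patients are selected on it. If the full protocol re-tests the cut-offs on Day −1 or Day 0, leave that sample out of the reference rate too.
2. Replace Day 0 or Day 1 by the mean of the pre-dose run-in samples as the plasma baseline. Show each patient's percentage fall from it against the within-patient run-in SD. Three samples in each of 12 adults give 12 × (3 − 1) = 24 degrees of freedom for a pooled SD.
3. Keep the stated proportion. Add, as a sensitivity result with all treated adults as denominator, the proportion also below both cut-offs at the next scheduled plasma sample.

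A confirmed proportion should not replace the stated one. That would give metabolic correction a second meaning beside the one used for dosing, and a patient held at a dose as corrected could then be reported as uncorrected.

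The cost is a little more analysis and a sensitivity figure that may be lower than the main one. No extra sample is needed, and the definition used for dosing is not changed.

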#### 2.8.3. Efficacy Data Analysis

The changes from baseline for all efficacy endpoints and outcomes will be calculated using data from the run-in period (Day −91 to Day 0) as the baseline. Absolute and percentage changes from baseline in BMI will be plotted. In addition, absolute and percentage changes from baseline in BMI will be recorded against plasma and urine concentrations of thymidine and deoxyuridine. The percentage of patients achieving at least the minimum threshold of weight gain will be presented by dose. Since juvenile patients in the juvenile cohorts will be developing (i.e., growing and maturing) during the study, changes in weight and other efficacy endpoints cannot be reliably attributed to EE-TP, and therefore their data will not be included in the main efficacy analyses, and will be analysed separately.

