From Day 78, the dose will remain at the dose that achieved metabolic correction during the initial treatment phase (pre-Day 78). If metabolic correction was not achieved, treatment will advance to Dose Level 3 (~58–65 × 10^10^ erythrocytes encapsulating ~70–90 U TP/10^10^ erythrocytes) for subsequent treatment cycles. It is planned that patients will receive EE-TP every 2–4 weeks ± 2 days until the end of the study. Dose frequency may be reduced (e.g., from every 2 weeks to every 3–4 weeks) for individual patients based on emerging safety, tolerability, efficacy, and pharmacodynamics data. The interval between doses will not be shorter than 2 weeks ± 2 days. In the advent of an increase in plasma metabolite levels, the frequency of dosing and/or dose level will be reviewed and adjusted accordingly.

The study will be flexible; continued pharmacodynamic assessment will enable dose optimisation and further inform dose response models and establish the therapeutic window for the treatment. A Patient Oversight Committee will perform ongoing reviews of safety, tolerability, efficacy, and available pharmacodynamic data to ensure the acceptability of continued dosing and/or dose progression for each patient. An overview of the dosing scheme is presented in Figure 3.

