#### 2.8.1. Safety Data Analysis

A baseline sign and symptom will be defined as an adverse event that starts after the patient has provided written informed consent and resolves prior to the first treatment cycle. It will also be defined as an adverse event that starts prior to the first treatment cycle and does not increase in severity after dosing. A treatment emergent adverse event will be defined as an adverse event that occurs post-dose or that is present pre-dose and becomes more severe post-dose. Treatment emergent adverse events will be summarised by dose level, maximum severity, and relationship to the study drug. The frequency of treatment emergent adverse events plus the number and percentage of patients experiencing a treatment emergent adverse event will be summarised by dose level, the Medical Dictionary for Regulatory Activities system organ class, plus preferred term. A frequency summary will be presented by day of onset across the multiple dosing period. 

Vital signs, serum biochemistry, haematology, and urinalysis data will be summarised by dose level, together with changes from the baseline. All serum biochemistry, haematology, and urinalysis data outside the clinical reference ranges will be listed by parameter and treatment. ECG data, including QTc, QTcB, QTcF, the PR and QT intervals, QRS duration, and heart rate, will be obtained directly from the 12-lead ECG traces. The ECG data will be summarised by dose level. Values for ECG parameters outside the clinical reference ranges will be indicated on the individual patient data listings. Physical examination and concomitant medication data will be listed.

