**Figure 2 jcm-08-01096-f002:**
[figure not shown]
Study Design Schematic. The overall study duration will be 31 months, comprising 28 days screening, 90 days run-in, 24 months open label treatment and 90 days post-dose follow-up. The first 4 treatment cycles will be administered every 21 days, with patients receiving Dose Level 1 for the first 2 treatment cycles. If metabolic correction is not achieved, the subsequent 2 treatment cycles will be administered at Dose Level 2. From treatment day 78, a flexible dosing approach will be employed to achieve metabolic correction, where administration will be at Dose Levels 1, 2 or 3, once every 2–4 weeks ± 2 days until the end of the study.

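### By-dose tables of correction, weight gain and adverse events sort patients by earlier metabolic non-response and unequal time at risk, so they cannot be read as dose-response

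*Protocol article*

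**What the plan says.** The dosing rule is in section 2.3 and the captions of Figures 2 and 3. The Figure 2 caption states: "The first 4 treatment cycles will be administered every 21 days, with patients receiving Dose Level 1 for the first 2 treatment cycles". It continues: "If metabolic correction is not achieved, the subsequent 2 treatment cycles will be administered at Dose Level 2". From Day 78, section 2.3 says that "the dose will remain at the dose that achieved metabolic correction during the initial treatment phase", and for the others: "If metabolic correction was not achieved, treatment will advance to Dose Level 3". Section 2.3 also lets later rises in metabolites prompt a review of dose level or frequency. Under the Figure 3 caption, a patient still uncorrected after cycle 6 is referred to the Independent Data Monitoring Committee.

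Three analyses are laid out by dose:
- Section 2.8.2: "The proportion of patients who achieve metabolic correction" is to be shown by dose.
- Section 2.8.3: "The percentage of patients achieving at least the minimum threshold of weight gain will be presented by dose".
- Section 2.8.1: "Treatment emergent adverse events will be summarised by dose level, maximum severity, and relationship to the study drug". The number and percentage of patients with an event are also given by dose level.

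On use of the data, section 2.3 says that continued pharmacodynamic assessment will "further inform dose response models and establish the therapeutic window for the treatment".

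**The concern.** A table by dose invites the reader to compare doses. Here the dose groups are formed by the outcome: a patient reaches Level 2 only by failing at Level 1, and Level 3 only by failing at both. The higher groups therefore hold the harder patients, and a patient who responds early never appears in them. Time at each level is also unequal, because early responders stay at a low level for up to two years while a patient who escalates twice passes through Levels 1 and 2 in weeks. A percentage of patients with at least one event rises with time at risk whatever the dose does. Activity left over from earlier infusions further blurs which level produced a correction.

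The trial means to learn about dose and the therapeutic window. With 12 adults and no control group, a misleading pattern across three small groups would be hard to recognise as an artefact.

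**Working it through.** The article states no figure for this point, so there is none to reproduce.

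**1. Time at each level.** The switch points are Day 0, Day 42 and Day 78 (section 2.3), and treatment lasts 24 months, taken as 730 days. A patient who escalates twice and stays at Level 3 spends:
- Level 1: 42 − 0 = 42 days
- Level 2: 78 − 42 = 36 days
- Level 3: 730 − 78 = 652 days, and 652/42 = 15.5

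A patient corrected at Level 1 spends 730 days there. One corrected at Level 2 spends 42 days at Level 1 and 730 − 42 = 688 at Level 2.

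**2. Adverse events at a flat rate.** Assume 1 event per patient-year at every level. P(at least one event) = 1 − exp(−d/365).
- d = 42: 10.9%; d = 36: 9.4%; d = 652: 83.2%; d = 688: 84.8%; d = 730: 86.5%.

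For a patient who escalates twice, the three levels read 10.9%, 9.4% and 83.2%. For an assumed cohort of 12 ending 6/3/3 on Levels 1/2/3:

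| | Level 1 | Level 2 | Level 3 |
|---|---|---|---|
| Patients ever treated | 12 | 6 | 3 |
| Patient-days | 6×730 + 6×42 = 4,632 | 3×688 + 3×36 = 2,172 | 3×652 = 1,956 |
| Expected events (days/365) | 12.7 | 6.0 | 5.4 |
| % with an event | (6×86.5 + 6×10.9)/12 = 48.7 | (3×84.8 + 3×9.4)/6 = 47.1 | 83.2 |

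With the same underlying rate, percentages rise 83.2/48.7 = 1.7-fold while event counts fall.

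**3. The exposure ratio depends on the mix.** Patient-months at Levels 1/2/3 for 12 adults, by number ending on each level:
- 0/0/12: 16.6, 14.2, 257.2 (Level 3 to Level 1: 15.5)
- 4/4/4: 107.0, 95.2, 85.7 (0.8)
- 8/2/2: 197.5, 47.6, 42.9 (0.2)

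**4. Metabolic correction with no dose effect.** Assume each patient has a fixed chance of correction at each step, drawn from Beta(0.8, 1.2), mean 0.40. Among those treated at each level, the expected proportion corrected is 0.8/2 = 40%, 0.8/3 = 27% and 0.8/4 = 20%, a falling pattern from selection alone. The cumulative version is 40%, 40 + 60×0.267 = 56%, and 56 + 44×0.20 = 65%, which rises with no dose effect. If all patients share the same 40% chance, the by-level table reads 40/40/40 and there is no distortion.

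A true effect can also be hidden. Assume a normal patient effect with SD 2 on the logit scale, intercept −0.4, and a shift of 0.5 per level. True correction over all patients is 44/52/59%, but the table among those treated reads 44/34/32%.

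**5. Weight gain by final dose with no dose effect.** Use the same patient effect, no dose shift, and let half of it drive the chance of reaching the weight threshold. The split by final dose is about 65/53/33%.

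**6. Carry-over.** Inputs are an erythrocyte half-life T of 19–29 days (Introduction), infusions 21 days apart, and mid-range activities of 39.5 (Level 1) and 59.5 (Level 2) U/10^10 erythrocytes from Table 2. Assume the enzyme decays with the cell. The fraction left after 21 days is r = 2^(−21/T): 0.465 for T = 19 and 0.605 for T = 29.

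Level 1 share just before the Day 63 infusion = 39.5(r² + r³) / [39.5(r² + r³) + 59.5r]:
- T = 19: 12.5/(12.5 + 27.7) = 31%
- T = 29: 23.2/(23.2 + 36.0) = 39%

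After the cycle 4 infusion adds 59.5: 12.5/99.7 = 13% and 23.2/118.8 = 20%. All parts decay together, so that share is unchanged up to Day 77.

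**The case against.** The tables are descriptive, and the article never says that they compare doses. The primary endpoint, mean BMI change at 24 months, is not split by dose. The sentence about dose-response models refers to pharmacodynamic assessment, not to the adverse-event or weight-gain tables. Administered activity is already calculated per cycle, BMI change is set against metabolite levels, and events are also summarised by day of onset. Denominators, dose attribution and exposure-adjusted rates commonly belong in a statistical analysis plan, which is not shown.

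Much of this stands. The absence of person-time is not in itself a finding. What remains is that the article itself chooses the by-dose layout, and its own dosing rule makes that layout unreadable as dose-response. Day of onset shows calendar pattern, not exposure per level.

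A reader might infer that exposure differs 15-fold between levels in general, so that toxicity will look strongly dose-related. The documents do not support that. The ratio needs a patient who fails twice and then stays at Level 3 to month 24, which is not assured given later dose review and the committee referral after cycle 6. In the 6/3/3 cohort Level 1 has the most exposure.

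A reader might also infer that the tables must give a false trend in a known direction. They need not: identical patients with one chance per level give no distortion, and selection and carry-over can pull correction at Level 2 in opposite directions. However, the Discussion expects the patients' data to be very heterogeneous, so the benign case is not the expected one.

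**Conclusion.** The point holds as a limit on what three planned tables can show. Dose level follows from earlier metabolic failure, so the tables sort patients by responsiveness and by time at risk. They can produce a false dose pattern or conceal a real one, with a direction that depends on patient heterogeneity, the denominator, and how many patients correct early.

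The mechanism differs by outcome. For adverse events it is mainly unequal time at risk: 1.7-fold in the illustrative cohort, and about 8-fold (83.2/10.9 = 7.6) only in the extreme case of patients who all escalate twice and stay at Level 3. For correction and weight gain it is selection by non-response. Carry-over is a secondary blur of roughly 13–20% after the cycle 4 infusion.

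The days per level follow from the document. The event rate, the cohort mix, the heterogeneity models and enzyme decay with the erythrocyte are assumptions. The primary endpoint is not affected. This should be changed, but it does not threaten the trial.

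**What to change.** Change the analysis and table shells only; the dosing rule is untouched.
- **2.8.1:** Beside the percentages, report patient-months at each level and event rates per patient-month, attributing each event to the dose held at onset.
- **2.8.2:** Show correction as a per-patient titration sequence. If a cumulative proportion is given, label it titration success and not dose-response, because it cannot fall. Base any dose-response statement on a within-patient model of metabolite level against administered activity, which the plan already calculates for each cycle.
- **2.8.3:** Report the percentage reaching the weight-gain threshold over all adults. Label any split by dose as a split by metabolic responsiveness, not a comparison of doses.

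The cost is slightly more programming. No extra data, visits or patients are needed.
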